**Methods/Design:**

We are conducting a multi-site randomised open trial of geriatrician-led admission avoidance hospital at home, compared with admission to hospital. We are recruiting older people with markers of frailty or prior dependence who have been referred to admission avoidance hospital at home for an acute medical event. This includes patients presenting with delirium, functional decline, dependence, falls, immobility or a background of dementia presenting with physical disease. Participants are randomised using a computerised random number generator to geriatrician-led admission avoidance hospital at home or a control group of inpatient admission in a 2:1 ratio in favour of the intervention. The primary endpoint ‘living at home’ (the inverse of death or living in a residential care setting) is measured at 6 months follow-up, and we also collect data on this outcome at 12 months. Secondary outcomes include the incidence of delirium, mortality, new long-term residential care, cognitive impairment, activities of daily living, quality of life and quality-adjusted survival, length of stay, readmission or transfer to hospital. We will conduct a parallel economic evaluation, and a process evaluation that includes an interview study to explore the experiences of patients and carers.

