### Eligibility criteria

We are recruiting patients who meet the following eligibility criteria for inclusion: (i) are 65 years and older, (ii) are willing and able to give informed consent for participation in the study, (iii) have been referred to the geriatrician-led admission avoidance hospital at home service and would otherwise require hospital admission for an acute medical event. The presence of a carer will not be a requirement for enrolment and will depend on the individual circumstances of the patient; this will be at the discretion of the clinician responsible for the patient, as is current clinical practice in each centre. Participants will be excluded if they have (i) an acute coronary syndrome (this includes myocardial infarction and unstable angina and is characterised by cardiac chest pain and associated with ECG changes), (ii) require an acute surgical assessment, (iii) have a suspected stroke, (iv) are receiving end of life care as part of a palliative care pathway, (v) refuse admission to the geriatrician-led admission avoidance hospital at home, or are considered by the clinical staff to be too high risk for home-based care, for example those who are physiologically unstable, who are at risk to themselves or if the carer reports hospital at home would not be acceptable, and (vi) patients living in a residential setting.

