#### Secondary outcomes

At 6 months follow-up we are measuring:Incident and persistent delirium as defined by the Confusion Assessment Method (CAM). The CAM is a brief questionnaire that has been extensively used in research for screening and case ascertainment purposes [9].Cognitive impairment with the Montreal Cognitive Assessment (MoCA), the normal range is from 30 to 26 [10].Activities of daily living, measured by the Barthel Index [11].MortalityNew long-term residential careLength of stay in admission avoidance hospital at home and inpatient admissionReadmission or transfer to hospitalHealth status (measured by the EuroQoL five dimension (EQ5D) instrument to produce a single index value for use in cost-effectiveness analysis) [12]Resource usePatient satisfaction using the Patient-Reported Experience questionnaire, developed by Picker Europe and used in the National Audit of Intermediate Care [13].We are also collecting data for each patient on ‘living at home’ (the inverse of death or living in a residential care setting) at 12 months follow-up.

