### Randomisation procedure and concealment of allocation

The unit of randomisation is the individual participant, who is randomly allocated using a 2:1 ratio (2 admission avoidance hospital at home: 1 inpatient admission) by a local member of the research team who accesses Sortition, the Oxford University’s Primary Care Clinical Trials Unit’s validated in-house online randomisation system. Telephone randomisation is used if sites do not have online access. A computer-generated randomisation sequence is used, and randomisation is stratified by centre, gender and by known cognitive decline [measured by the Informant Questionnaire on Cognitive Decline in the Elderly (IQCODE)] [14]. We have opted for a 2:1 randomisation ratio to deal with the concern expressed by clinical leads that a 1:1 randomisation ratio would place unmanageable pressure on the inpatient services. The success of randomisation is being measured by the number declining to be randomised or withdrawing immediately after randomisation.

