### Analysis

We will analyse the data using an intention-to-treat analysis and based on a mixed effect model adjusting for recruitment centre (random effects) and individual patient characteristics. For the primary outcome of living at home 6 months, the primary analysis we will use a mixed-effect logistic regression model including data available on all randomised patients at 6 months and 12 months follow-up, adjusting for recruitment centre, gender, and IQCODE score at baseline. In the model, participants and centres will be fitted as random effect, and time and treatment as fixed effect. We will fit an interaction term between time and intervention group so that possible differences of intervention effect could be assessed at each time point. Although, the method has the advantage of implicitly accounting for the data missing at random mechanism, we will also assess the impact of missing data on the primary analysis by carrying out sensitivity analyses based on imputing (multiple imputation) the missing values. We will use similar models for all binary outcomes (presence of delirium, cognitive impairment, etc.), and will use equivalent models for continuous outcomes (e.g. normal distribution). We expect length of stay to be highly skewed so other parametric models might be required for this, and in the case of poor fit we will use simple non-parametric tests (non-adjusted) for this outcome. We have planned one subgroup analysis of the effect of care setting (home versus hospital) on the incidence of delirium in people who are cognitively impaired (defined by the MoCA) [10].

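### The 6-month cognitive outcome is planned as impaired yes/no, which loses power that the MoCA score, already collected, would keep

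*Protocol article*

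**What the plan says.** - **Form of the outcome.** In the protocol article, Analysis, the logistic mixed model of the primary outcome is extended to other endpoints: "We will use similar models for all binary outcomes (presence of delirium, cognitive impairment, etc". The same sentence goes on to say that the authors "will use equivalent models for continuous outcomes (e.g. normal distribution", without naming cognition there.
- **Measure.** Secondary outcomes lists "Cognitive impairment with the Montreal Cognitive Assessment (MoCA), the normal range is from 30 to 26". This is the only MoCA boundary in the document, and no section calls it the analysis cut-off.
- **Second use of the MoCA as a classifier.** The one planned subgroup analysis examines the effect of care setting "on the incidence of delirium in people who are cognitively impaired (defined by the MoCA", again without a cut-off.
- **Population.** The abstract's Methods/Design paragraph says: "This includes patients presenting with delirium, functional decline, dependence, falls, immobility or a background of dementia presenting with physical disease". Under Randomisation procedure, "randomisation is stratified by centre, gender and by known cognitive decline", measured by the IQCODE.
- **Data.** Table 1 schedules the MoCA at baseline and at 6 months.

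**The concern.** Cognitive impairment is a named secondary objective. Naming it as a binary outcome is a stated choice of method, not a detail left open. A yes/no MoCA outcome needs a cut, and the lower end of the normal range is the only candidate in the text. Someone with background dementia who scores 12 at entry is impaired at 6 months whether the score then is 8 or 18. The split records neither that decline nor that improvement.

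The more participants lie well below the cut, the less the comparison can show. A non-significant difference in the proportion impaired could then be read as no cognitive effect of care setting, when the scores in the database might have shown one.

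**Working it through.** **No figure to reproduce.** The protocol gives no expected impairment rate, MoCA distribution or effect size for cognition. Everything numerical below is an assumption except the 0-30 scale with its 26-30 normal range, the 2:1 allocation and the two-sided 5% level.

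**Step 1: information kept by a split.** For a normally distributed score with a proportion p below the cut, the share of information kept is φ(z_p)² / [p(1 − p)]. At p = 0.5 this is 0.399² / 0.25 = 0.64. It is 0.49 at p = 0.8, 0.34 at 0.9 and 0.22 at 0.95. There is a loss at every rate, and it is severe when nearly everyone is below the cut.

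**Step 2: one scenario by hand.** Assume 700 v 350 assessed, SD 6, mean 18, a true 1-point shift and whole-number scores, so that impaired means below 25.5.
- Controls impaired: Φ(7.5/6) = 0.894. Intervention: Φ(6.5/6) = 0.861. Difference 0.034.
- Pooled proportion (0.894 + 2 × 0.861)/3 = 0.872. SE = √[0.872 × 0.128 × (1/700 + 1/350)] = 0.0219. Ratio 1.54; power Φ(1.54 − 1.96) = 34%.
- Score, unadjusted: SE = 6 × √(1/700 + 1/350) = 0.393. Ratio 2.55; power Φ(2.55 − 1.96) = 72%.
- Score, adjusted for baseline with correlation 0.6: SE = 0.393 × √(1 − 0.36) = 0.314. Ratio 3.18; power Φ(3.18 − 1.96) = 89%.

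Part of the gap between 34% and 89% is baseline adjustment, not the split. The fair comparison adjusts both analyses.

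**Step 3: both analyses adjusted for baseline MoCA.** This is a simulation with scores rounded and clipped to 0-30, a 1-point shift and no centre effect. It compares logistic regression on a score below 26 with linear regression on the score. The binary figures come from two separate sets of runs; set B used 2,000 simulated trials per row (Monte Carlo SE at most about 1.1 points).

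| Mean MoCA | Controls below 26 | Binary, set A | Binary, set B | Score (set B) |
|---|---|---|---|---|
| 15 | 96% | 26% | 21% | 90% |
| 18 | 89% | 37% | 41% | 90% |
| 20 | 82% | 47% | 50% | 88% |
| 22 | 72% | 53% | 59% | 88% |
| 24 | 60% | 65% | 62% | 85% |

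The two sets differ by 3 to 6 points, which does not change the reading. For a 1.5-point shift, the adjusted binary analysis reaches about 46%, 72% and 84% at means 15, 18 and 20, against over 99% for the score.

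**Step 4: other numbers assessed.** With neither analysis adjusted and a shift of 0.2 SD:

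| Assessed | Score | Binary: 50% impaired | 80% | 90% | 95% |
|---|---|---|---|---|---|
| 1350 | 93% | 79% | 70% | 55% | 39% |
| 800 | 76% | 57% | 47% | 35% | 24% |

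The direction is the same throughout; only the size changes.

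**The case against.** **The cut of 26 is inferred.** That is correct, and the working depends on it. A different cut would change the share impaired and so the size of the loss, but Step 1 shows that no cut avoids one.

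**The analysis plan may analyse the score.** This is a condensed article, and cut-offs are commonly left to that plan. The missing cut-off is therefore not the complaint. What stands is that the article names the binary form and does not name the score.

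**The population is mixed.** Delirium and background dementia stand beside falls, immobility, functional decline and dependence. Participants must be those who "are willing and able to give informed consent for participation in the study", although Data collection, management and analysis mentions consultees. A subgroup defined by impairment also presupposes that some people are not impaired. All this is fair, and it is why the milder means of 22 and 24 are shown.

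**Stronger readings.** A reader might infer that most participants cannot change category, that the objective is barely testable, or that a null result is close to guaranteed. The document does not support these:
- It gives no MoCA distribution.
- Baseline scores are taken during acute illness, and some people may return to the normal range by 6 months.
- The planned comparison is the proportion impaired in each arm at 6 months, not a change of category. Even with 90% of controls impaired, a difference of 5.4 points (1350 assessed) or 7.3 points (800 assessed) is detectable with 80% power.

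**The proportion impaired is clinically readable.** True, and it can still be reported.

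**Conclusion.** The concern holds as a loss of efficiency in one secondary outcome. The protocol names a binary form for cognition in a population where a substantial share may already be below the only boundary it gives. Under the stated assumptions (SD 6, correlation 0.6, 1050 assessed, 1-point shift, cut at 26), the split lowers power from about 85-90% to between about a quarter, or slightly less, at mean 15 and just under two thirds at mean 24. The loss appears at every assumed mean; its size in this trial cannot be known from the document. It should be changed, but it leaves the primary outcome and the sample size untouched.

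**What to change.** In Secondary outcomes and Analysis, define the cognitive outcome as the MoCA total score at 6 months. Analyse it with the mixed model already planned for continuous outcomes, adjusted for baseline MoCA, centre, gender and IQCODE. Take cognitive impairment out of the list of binary outcomes. Report the proportion impaired in each arm as a supporting description at a cut fixed before analysis, and state whether the delirium subgroup uses the same cut. If the analysis plan already does this, aligning the article's wording is enough.

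The cost is wording only: the scores are collected at both times, and recruitment was still under way when the article was written.

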**Fig. 2 Fig2:**
[figure not shown]
Participant timeline

At the 6-month follow-up point we collect data from all patients on mortality, new long-term residential care, cognitive impairment, activities of daily living, quality of life, length of stay, readmission or transfer to hospital, and on the number, type and duration of hospitalisations, the use of outpatient and day-case services, the use of community-based health care services including general practitioner consultations and practice-based nursing, medications, respite care, social care including admission to residential or nursing home, and amount of informal care received over the preceding 6 months. Unit costs will be attached to these resource volumes, using National Health Service (NHS) reference costs, Unit Costs of Health and Social Care (PSSRU), and other national data sources. We will collect the costs of the admission avoidance hospital at home intervention in collaboration with providers, and include training time and other elements. This is likely to vary between centres and we aim to collect cost information from all participating centres if possible. At 12 month follow-up we will collect data on living at home (Table 1).

**Table 1 Tab1:** Case report form

	Study period					
	Baseline	Day 3	Day 5	1 month	6 month	12 month
ENROLMENT						
Eligibility screen	X					
*Informed consent*	X					
*Screening log*	X					
Randomisation	X					
ASSESSMENT						
Assessment form	X	X	X	X	X	X
*Demographics*	X					
*Presenting problem*	X					
*Place of assessment*	X	X	X	X	X	X
*Patient status* (*‘living at home’*)		X	X	X	X	X
*Subsequent admissions*				X	X	
Adverse event log		X	X	X	X	X
QUESTIONNAIRES						
Barthel Index of Activities of Daily Living	X				X	
Confusion Assessment Method (CAM)	X	X	X	X		
Charlson Co-morbidity Index	X				X	
Health Service Use Questionnaire	X				X	
Short Form of the Informant Questionnaire on Cognitive Decline in the Elderly (Short IQCODE)	X					
Montreal Cognitive Assessment (MoCA)	X				X	
EuroQol five-dimension five-level (EQ-5D-5 L)	X				X	
Patient feedback form				X		
Difficulties in Questionnaire completion Form	X	X	X	X	X	
MISCELLANEOUS						
Death form	Completed on patient death					
Discontinuation form	Completed when a patient withdraws or is lost to follow-up					

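### Continuous secondary outcomes inherit a covariate list without their own baseline value, which costs precision, and a two-time-point model that does not match their single follow-up

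*Protocol article*

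**What the plan says.** The Analysis section opens with a general statement that the analysis is "based on a mixed effect model adjusting for recruitment centre (random effects) and individual patient characteristics". For the primary outcome it then becomes specific:

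- Data: "including data available on all randomised patients at 6 months and 12 months follow-up".
- Covariates: "adjusting for recruitment centre, gender, and IQCODE score at baseline".
- Random and fixed effects: "participants and centres will be fitted as random effect, and time and treatment as fixed effect".
- Interaction: "We will fit an interaction term between time and intervention group".

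It next extends similar models to the binary outcomes, among which it counts cognitive impairment, and "will use equivalent models for continuous outcomes (e.g. normal distribution"). The distribution is the only change it mentions.

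The schedule for the continuous measures differs from that of the primary outcome. In Table 1 the row for "Barthel Index of Activities of Daily Living" is marked at baseline and 6 months only, and so are the rows for MoCA and EQ-5D-5L. The section on data collection confines the 12-month visit to the primary outcome. The same section allows a two-stage baseline for patients who appear burdened. In that case Barthel, MoCA and EQ-5D-5L are completed shortly after allocation. The Economic analysis section derives QALYs by straight-line interpolation between baseline and 6-month EQ-5D and mentions no adjustment for baseline utility.

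**The concern.** The primary model suits the primary outcome. It has two follow-up records per person, so a participant effect and a time-by-treatment term have something to estimate. It needs no baseline value of the outcome, because people already living in a residential setting are excluded and everyone starts at home.

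Neither condition holds for Barthel or EQ-5D-5L. They have one follow-up record, and they have a baseline score that varies between people and would ordinarily be expected to predict the 6-month score. Two things follow if the model is carried over as described. Some of its terms have no role, and a useful covariate that is already being collected is not among those named. At stake is the width of the intervals for activities of daily living and quality of life, and the precision of the QALY difference.

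**Working it through.** The article states no power, standard deviation or correlation for any continuous secondary outcome, so there is no figure of its own to reproduce.

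**1. The terms that one follow-up cannot support**

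With one record per person, the variance of an observation is (centre variance) + (participant variance) + (residual variance). Only the sum of the last two can be estimated. This was checked on one simulated data set (1350 people, 8 centres, 2:1 allocation). The total of the two was fixed at 1 and the participant share set to 0, 0.25, 0.5, 0.75 and 0.95.

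- The log-likelihood was -1846.697 at every split.
- The treatment estimate was 0.0806 with standard error 0.0580 at every split.

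With a single time point, the time column equals the intercept and the time-by-treatment column equals treatment. A design with intercept, treatment, gender, IQCODE, time and time-by-treatment has 6 columns but rank 4. Dropping the two redundant columns and the participant effect leaves the treatment result as it was.

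**2. The omitted baseline value**

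Let r be the correlation between the baseline and 6-month values. It is not in the article; 0.3 to 0.7 is assumed. Adjustment multiplies the variance of the treatment effect by 1 - r², so the standard error falls by the factor √(1 - r²). The interval without adjustment is wider by 1/√(1 - r²) - 1.

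The difference detectable with 90% power at two-sided 0.05, in SD units, is (1.960 + 1.282) × √(1/n_control + 1/n_intervention) × √(1 - r²). To set a scale, take the 1350 participants of the Sample size section, split 450 and 900: 3.2415 × √(1/450 + 1/900) = 3.2415 × 0.05774 = 0.187 SD without adjustment. With 70% analysed (an assumption; 315 and 630) it is 3.2415 × 0.06901 = 0.224 SD.

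| r (assumed) | 1 - r² | SE factor | CI wider if omitted | Detectable, 1350 analysed | Detectable, 945 analysed |
|---|---|---|---|---|---|
| no adjustment | 1 | 1 | – | 0.187 SD | 0.224 SD |
| 0.3 | 0.91 | 0.954 | 4.8% | 0.179 SD | 0.213 SD |
| 0.5 | 0.75 | 0.866 | 15.5% | 0.162 SD | 0.194 SD |
| 0.7 | 0.51 | 0.714 | 40.0% | 0.134 SD | 0.160 SD |

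**3. Allowing for IQCODE**

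The table compares against no covariates, whereas the stated model already has gender, IQCODE and centre. In the simulated data, where baseline was made to depend on IQCODE and had a slope of 0.6 on the outcome, adding it to those three covariates reduced the standard error from 0.0549 to 0.0453. The ratio is 0.0453/0.0549 = 0.82. The gain shrinks to the extent that IQCODE explains the outcome, but it need not vanish.

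**4. QALYs**

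For a survivor, straight-line interpolation over half a year gives 0.5 × (u0 + u6)/2 = 0.25 × u0 + 0.25 × u6. Here u0 and u6 are the baseline and 6-month utilities. A chance difference D in mean baseline utility therefore adds 0.25 × D to the unadjusted QALY difference, whatever happens at 6 months.

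**The case against.** The strongest case against is that this rests on wording in a condensed article whose analysis plan is not shown. Gender and IQCODE are listed in the sentence about the primary outcome. The general statement before it speaks only of patient characteristics, and a baseline Barthel score is one. Equivalent need not mean identical, and since no 12-month Barthel data exist the model must be adapted somehow. This stands in part: the article is silent on baseline adjustment and does not rule it out. But the only characteristics it goes on to name are gender and IQCODE, and the only adaptation it names is the distribution.

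One possible adaptation enters baseline and 6 months as two repeated outcomes, which would identify the participant effect. That also stands as a possibility. The article, however, defines its model on follow-up data. If that layout is intended it should be stated, together with whether the arm means are constrained to be equal at baseline. If they are left free, the interaction estimates the difference in change scores, with relative variance 2(1 - r). This is 1.4, 1.0 and 0.6 at r = 0.3, 0.5 and 0.7, against 0.91, 0.75 and 0.51 for covariate adjustment.

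A reader might infer that the model cannot be fitted, or will not converge. The check does not support this: a nuisance variance is unidentified and two columns are redundant, while the treatment estimate and standard error are unaffected. A reader might also infer bias from baseline imbalance. Randomisation keeps the unadjusted estimate valid, and its interval already reflects chance imbalance. Nor can MoCA simply be counted among the continuous outcomes, because the Analysis section lists cognitive impairment as binary.

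Finally, conditioning on baseline scores has a small risk of its own, since some may be recorded after allocation in an open trial. That objection is sound and is met in the fix.

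**Conclusion.** The point holds as one of efficiency in secondary outcomes. The named covariates leave out the baseline Barthel and EQ-5D-5L scores that the trial collects. The unadjusted interval is about 5%, 15% or 40% wider than necessary at an assumed r of 0.3, 0.5 or 0.7, and by less where IQCODE already carries some of the same information. Baseline is taken during acute illness, so the lower end of the range cannot be excluded. The redundant participant and time terms are a mismatch of specification to schedule, with no effect on the treatment result. The primary analysis is untouched. The article supports neither a claim of bias nor a claim that the analysis will fail, and an analysis plan that is not shown may already settle the covariates.

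**What to change.** State in the analysis plan, before unblinded data are examined:

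- For Barthel and EQ-5D-5L, and for MoCA if it is analysed as a score, use a linear model of the 6-month value. Include treatment, the outcome's own baseline value, gender, IQCODE and centre as a random effect, with no participant or time terms.
- Adjust the QALY difference for baseline EQ-5D utility.
- Fill missing baseline values by a simple imputation that does not use allocation, so that no participant is dropped.
- Because the two-stage approach allows some baseline scores to be recorded after randomisation, add a sensitivity analysis that either omits the baseline covariate or treats those late values as missing.

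This takes a few sentences and no new outcome measures. Identifying the late values requires that the completion date of each baseline questionnaire be available. The cost is one additional sensitivity analysis per outcome.

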### Setting and sample

Participants are being recruited from primary care or an acute hospital-based assessment unit in Aneurin Bevan University Health Board; Bradford Teaching Hospitals NHS Foundation Trust; Guy’s and St Thomas’s NHS Foundation Trust, London; Royal Devon and Exeter NHS Foundation Trust; Monklands Hospital, NHS Lanarkshire; St John’s Hospital, NHS Lothian; Southern Health and Social Care Trust, Northern Ireland; Belfast Health and Social Care Trust, Northern Ireland. We are recruiting older people with frailty who require a hospital admission due to an acute change in health. This might be due to acute functional deterioration, delirium, falls and complex comorbidity. There is no simple accepted definition of this population due to variation in the acute presenting illness. However, it is agreed that the degree of prior disability is important and that attempts to define this group should be problem-based [8]. We will describe patients recruited to this trial according to functional dependence, cognitive impairment, comorbidity, history and/or presence of delirium and presenting complaint (such as falls, reduced mobility, confusion, carer strain).

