### Statistical methods

#### Sample size

We calculated the sample size for the primary outcome ‘living at home’ (the inverse of death or living in a residential care setting) at 6 months follow-up, for a 2:1 randomisation ratio with two-thirds randomised to admission avoidance hospital at home and one-third to inpatient admission. Several sources informed our estimate of effect size, these included an audit of 750 patients who received admission avoidance hospital at home in Lanarkshire, and the summary estimate from a Cochrane Review of admission avoidance hospital at home that was published in 2008 [16]. Our proposed study effect estimate is based on a control group (inpatient admission) event rate at 12 months of 50% living in a residential setting, with a 10% reduction to 40% in the admission avoidance hospital at home group, equal to a relative risk of 0.8 which lies towards the top end of the 95% confidence interval (CI) for the pooled estimate reported in the Cochrane Review [16]. We have calculated that to achieve 90% power at a significance level of 0.05, we will need to recruit 1350 participants to detect a 10% absolute difference. The estimated recruitment rate allows 15% attrition resulting in a projected sample size of 1552. We have re-examined the sample size calculation using an estimate of the intra-cluster correlation (ICC) of 0.005, this would provide 88% power to detect the assumed effect size of RR = 80%, for a two-tailed alpha of 0.05.

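### The fallback test for length of stay drops the stratification factors, so it is conservative and loses power if stay differs strongly between centres

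*Protocol article*

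**What the plan says.** The Analysis section of the protocol opens with a general rule: the intention-to-treat analysis will be "based on a mixed effect model adjusting for recruitment centre (random effects) and individual patient characteristics". Equivalent models are to be used for the continuous outcomes.

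Length of stay is then treated separately, in two steps. First: "We expect length of stay to be highly skewed so other parametric models might be required for this". Second, should those models fail: "in the case of poor fit we will use simple non-parametric tests (non-adjusted) for this outcome".

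Under Randomisation procedure and concealment of allocation, the protocol states that "randomisation is stratified by centre, gender and by known cognitive decline", the last of these being measured by the IQCODE. Length of stay, in hospital at home and as an inpatient, is listed under Secondary outcomes.

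**The concern.** Stratified randomisation balances the arms within each centre. Differences between centres then add spread to the pooled data but do not add error to the comparison of arms. A test that ignores centre counts that spread as error. Its standard error is too large, its true type I error falls below the nominal 5%, and it gives up power. The same argument applies to gender and IQCODE if they predict stay.

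The protocol does not merely leave this open. It writes down an unadjusted test, which departs from its own rule a few sentences earlier. At stake is the sensitivity of one secondary comparison, and only if the fallback is reached. No false-positive risk arises.

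**Working it through.** **Plan's own figure.** There is none to reproduce. The protocol gives no effect size, standard deviation, ICC or power for length of stay. Its sample-size figures, including an ICC of 0.005, concern the primary outcome.

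**Inputs from the protocol**
- Centres: 8, counted from the list under Setting and sample.
- Allocation: 2:1 (Sample size).
- Number of patients: 1350, the pre-attrition figure in Sample size, used here only as a working size.
- Two-sided alpha 0.05 (Sample size), carried over to this outcome.

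**Assumed inputs**
- Equal centres: 1350/8 rounds down to 168 each, so 8 × 168 = 1344 patients, with 112 v 56 in each centre (896 v 448 in all).
- Log-normal stay, rounded up to whole days, with within-centre SD 1.0 on the log scale.
- Treatment effect −0.17 on the log scale, a ratio of exp(−0.17) = 0.84, chosen to give about 80% power.
- Between-centre variance set by ICC = s²/(s² + 1), with the ICC varied from 0 to 0.30.
- Gender and IQCODE effects were not simulated.

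**Step 1: simulation.** 2000 simulated trials per cell. The Monte Carlo standard error of a power near 80% is √(0.8 × 0.2/2000) = 0.9 points.

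| ICC | Type I error, unadjusted rank test | Power, unadjusted | Power, centre-stratified (van Elteren) | Loss (points) |
|---|---|---|---|---|
| 0 | 5.2% | 81.4% | 80.9% | −0.5 |
| 0.005 | 4.9% | 81.0% | 81.0% | 0.0 |
| 0.02 | 4.8% | 79.9% | 80.6% | 0.7 |
| 0.05 | 4.8% | 80.0% | 80.2% | 0.2 |
| 0.10 | 3.4% | 78.4% | 80.2% | 1.8 |
| 0.20 | 2.6% | 75.0% | 81.0% | 6.0 |
| 0.30 | 1.6% | 69.8% | 81.2% | 11.4 |

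A linear model on log stay adjusted for centre gave 81% to 83% power throughout.

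**Step 2: closed-form check.** With balance within centres, the true variance of the comparison is about (1 − ICC) times the variance that the unadjusted test assumes. Hence:
- type I error ≈ 2 × Φ(−1.96/√(1 − ICC));
- power ≈ Φ(d − 1.96/√(1 − ICC)), where d = 1.96 + Φ⁻¹(0.809) = 2.834 gives the stratified test 80.9% power.

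Results:
- ICC 0.005: 1.96/0.9975 = 1.965; error 4.9%; power 80.8%; loss 0.1 points.
- ICC 0.05: 1.96/0.9747 = 2.011; error 4.4%; power 79.5%; loss 1.4.
- ICC 0.10: 1.96/0.9487 = 2.066; error 3.9%; power 77.9%; loss 3.0.
- ICC 0.20: 1.96/0.8944 = 2.191; error 2.8%; power 74.0%; loss 6.9.
- ICC 0.30: 1.96/0.8367 = 2.343; error 1.9%; power 68.8%; loss 12.1.

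This agrees with the simulation in direction and closely in size.

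**Step 3: other inputs.** With within-centre SD 0.9, effect 0.15 and 4000 runs, unadjusted v stratified power was 80.1% v 79.7% at ICC 0.005, 80.1% v 80.3% at 0.02, 79.3% v 80.3% at 0.05 and 76.9% v 79.6% at 0.10. Further runs gave losses of about 8 points at ICC 0.24 and 16 at 0.38.

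**The case against.** The strongest reply is that this is a conditional second step for one secondary outcome, that the unadjusted test is valid, and that the loss may be nil. All of that stands. The only ICC in the protocol is 0.005, for the primary outcome, and at that value no loss can be detected. The Interventions section also says that centres agreed protocols to keep usual care comparable. Against this, the research objective expects provision to vary between settings, and some elements of hospital at home are available only at some sites. Centre differences in stay are therefore plausible, but their size is unknown.

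A reader might be tempted to infer more than the protocol supports:
- **That the fallback will probably be used because skew is expected.** Expected skew leads first to other parametric models. The unadjusted test follows only if those fit poorly.
- **That no effect estimate will be reported, leaving nothing usable for decisions.** The text names a type of test and is silent on estimates, which is not the same as ruling them out. The Economic analysis section also costs inpatient stays and hospital at home durations separately, with bootstrap uncertainty.
- **That the missing definition of poor fit is a fault.** An article can leave that to the analysis plan.
- **That deaths during the episode should be ranked worst.** The protocol does not say how such deaths are scored. The question affects parametric models equally, and ranking deaths worst would change the quantity being estimated. It is a separate choice.

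What survives the reply is that the protocol explicitly chose to leave out factors it randomised by, and that keeping them costs essentially nothing.

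**Conclusion.** The point holds as a minor, near-costless improvement. If reached, the fallback drops centre, gender and IQCODE, against the stratified design and the protocol's own adjusted-analysis rule. The test remains valid but conservative: simulated type I error is about 4.9% at ICC 0.005, 3.4% at 0.10 and 1.6% at 0.30. The power loss is negligible up to an ICC of about 0.05 (at most about 1 point by simulation, 1.4 by formula). It is about 2 to 3 points at 0.10, 6 to 8 at 0.20 to 0.24, and 11 or more from 0.30.

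These figures rest on assumed log-normal stays, equal centres, additive centre effects and about 80% baseline power. Because the protocol gives no between-centre variation for stay, an unconditional claim that power is wasted is not supported.

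**What to change.** Either of two changes is enough:

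1. Replace the unadjusted test with a rank test stratified at least by centre (van Elteren), and report a stratified shift estimate in days with a 95% confidence interval.
2. Name a skew-tolerant model that keeps the stratification factors, for example a gamma or log-link model with robust or bootstrap intervals, so that no unadjusted fallback is needed. The protocol's step of other parametric models already allows this.

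Stratifying by centre alone is a reasonable minimum. If cognitive decline is taken as two levels (an assumption), crossing all three factors gives 8 × 2 × 2 = 32 strata, or about 1350/32 ≈ 42 patients each on average, and fewer in small centres.

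The cost is a change of wording and slightly more programming. No further data or patients are needed. Recruitment is described as ongoing, so the change could be made before analysis. In the simulations, stratifying when centres did not differ gave 80.9% power against 81.4%, which is within simulation error.
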